#### 1.1.3 Examination of the evidence for the ergogenic properties of rHuEPO in cyclists

The evidence for the effect of rHuEPO in well trained athletes is in fact sparse until today. A qualitative systematic review of the available literature was performed in 2012 to examine the evidence for the performance enhancing properties of rHuEPO in cyclists.

The review demonstrated that the characteristics of the study populations differed from the population suspected of rHuEPO abuse. rHuEPO studies often used untrained or moderately trained cyclists. It cannot be assumed that effects found in these studies automatically apply to well-trained cyclists. Most studies used a small number of untrained subjects and the quality of the research was often questionable. In these studies, the main studied effect was the maximal oxygen carrying capacity of blood ( $V_{O2, max}$ ) which only has a remote connection to performance in endurance sports, especially in well-trained athletes. This is in line with the knowledge that multiple factors affect performance, in which oxygen carrying capacity of the blood becomes less relevant when other factors become rate-limiting. Endurance performance may be better correlated with submaximal exercise factors. There a number of findings that support this last notion. Firstly, research into training for endurance performance shows that moderately trained athletes are able to improve  $V_{O2, max}$  by interval and/or intensive training, whereas these training regimens do not improve  $V_{O2, max}$  in well-trained athletes. After initial years of training, these well-trained athletes maintain a plateau in their  $V_{O2, max}$ , but continue to improve their performance. This shows that other factors have to play an important role in endurance performance.

Secondly, long exercise times during consecutive days, with the finish line as a known end-point (contrary to the 'open end' of time-to-exhaustion tests) makes it crucial for cyclists to distribute their power during a race. This, combined with (team) tactics, the terrain and the effects of drag force, means that cyclists work for only a small amount of time at their peak intensities ( $V_{O2, max}$ ), the rest of the time they will work at sub-maximal intensities where submaximal exercise factors are more important.

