#### 1.4.4 Study design

This study will be conducted in accordance with guidelines from the International Conference on Harmonization (ICH) on current Good Clinical Practice (GCP) and the ethical principles that have their origins in the Declaration of Helsinki.

In order to investigate the effects and safety of NeoRecormon in well-trained cyclists a randomized, double-blind, placebo-controlled study is most appropriate.

The total study period will be 17 weeks. Within 6 weeks prior to the start of the treatment, subjects will undergo a medical screening. A ramp exercise test on a cycle ergometer will be performed directly after the screening to familiarize with the test and to determine the subject's maximal power output. A second ramp and TTE exercise test will be performed for baseline measurements within 2 weeks prior to the first administration, but after the screening. During the 8 week treatment period subjects will be administered with NeoRecormon or placebo once a week. During the treatment period subjects will follow their usual training program and will perform a ramp exercise test (see appendix 5) every two weeks. In the 7th treatment week the subjects will also perform a TTE

exercise test (see appendix 5). After the treatment period subjects will participate in a competition (see appendix 6). A follow-up visit will be scheduled, 30 days after the last dose.

Please refer to the visit and assessment schedule for a more detailed description of the study design (see Table 1).

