### **3.1.4 Competition**

After the treatment period subjects will participate in a competition. The competition is designed in a way that it closely resembles real racing conditions and complies with the required performance duration. During the competition physiological parameters will be measured. Before and after the competition blood will be collected at predetermined stages.

Please refer to appendix 6 for a detailed description of the competition.

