### *Competition*

Exercise parameters that will be measured and calculated during the competition:

- Result in the race
- Total time of the race
- Power (W)
- Heart rate (bpm)
- Systolic blood pressure (mmHg)
- Diastolic blood pressure (mmHg)

Before and after the competition blood will be collected to determine if certain protein concentrations are influenced by NeoRecormon such as:

- Lactate
- Tissue plasminogen activator
- Creatinine phosphokinase
- C-reactive protein
- Coagulation and activation markers (D-Dimer, F1+2, p-Selectin, e-Selectin, ThromboxaneB2, bTG, PF4, thrombomodulin)

In urine:

- Proteinuria

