## 9.9 Efficacy endpoints

### 9.9.1 Efficacy

The final analysis will be preceded by a blind data review which consists of individual graphs per visit by time of all efficacy measurements by time. The graphs will be used to detect outliers and measurements unsuitable for analysis. The efficacy parameters will be listed by treatment, subject, visit and time. Individual graphs by time will be generated.

All measured PD endpoints will be summarised (n, mean, SD, SEM, median, Min and Max values) by treatment and time, and will also be presented graphically as mean over time, with standard deviation as error bars. All efficacy endpoints will be summarised (mean, SD, SEM, median, Min and Max values) by treatment, and will also be presented graphically as mean in a bargraph, with standard deviation as error bars.

Parameters will initially be analyzed without transformation, but if the data suggest otherwise, log-transformation may be applied. Log-transformed parameters will be back-transformed after analysis where the results may be interpreted as percentage change.

To establish whether significant treatment effects can be detected on the measured efficacy parameters, each parameter that is measured repeatedly will be analyzed with a mixed model analysis of covariance (ANCOVA) with treatment, time and treatment by time as fixed factors and subject, subject by treatment and subject by time as random factors and the (average) baseline measurement as covariate. Parameters that are only measured at baseline and at the end of the treatment phase will be analysed with a one-way ANCOVA with treatment and baseline as covariate.

Single measured efficacy parameters will be analyzed with an unpaired t-test.

The Kenward-Roger approximation will be used to estimate denominator degrees of freedom and model parameters will be estimated using the restricted maximum likelihood method.

The general treatment effect and specific contrasts will be reported with the estimated difference and the 95% confidence interval, the least square mean estimates and the p-value. Graphs of the Least Squares Means (LSM) estimates over time by treatment will be presented with 95% confidence intervals as error bars, as well as change from baseline LSM estimates.

The following contrasts will be calculated within the model:

- NeoRecormon - Placebo

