## 18 APPENDIX 6 – COMPETITION

Subjects will climb the Mont Ventoux in an open course via Bédoin after a 150km closed course. A blood sample of each subject will be collected in Bédoin (at the end of the closed course) and at the finish. A power meter will be incorporated into each bike.

[figure not shown]

Figure 2. Detailed description of the Mont Ventoux climb via Bédoin.

| BÉDOIN              |         |
|---------------------|---------|
| WIKI                | Bédoin  |
| STARTING ALTITUDE   | 290 m   |
| FINISHING ALTITUDE  | 1912 m  |
| LENGTH              | 21.5 km |
| DIFFERENCE IL LEVEL | 1620 m  |
| AVERAGE GRADIENT    | 7.5 %   |
| MAXIMUM GRADIENT    | 12.5 %  |

**Figure 3.** Characteristics of the Mont Ventoux climb via Bédoin.

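### Race outcomes are compared by an unadjusted t-test although a pre-dose Pmax/kg is available for every subject, which gives up precision

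*Protocol*

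**What the plan says.** Protocol section 9.9.1 sorts efficacy parameters into three classes. Those measured repeatedly get a mixed-model ANCOVA with baseline as covariate. Those measured at baseline and at the end of treatment get a one-way ANCOVA with baseline. For the rest, "Single measured efficacy parameters will be analyzed with an unpaired t-test".

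The race belongs to the third class. Section 3.1.4 places it after dosing ("After the treatment period subjects will participate in a competition"), and no race is run before dosing. Section 6.1 lists "Result in the race", "Total time of the race", power, heart rate and blood pressure among its outcomes. No other section gives the race a different model. Synopsis section 19 repeats only the two baseline-adjusted models, and the statistics paragraph in Appendix 5 concerns the exercise tests.

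A baseline measure of fitness exists. Section 1.4.4 states: "A second ramp and TTE exercise test will be performed for baseline measurements within 2 weeks prior to the first administration". Section 6.1 derives maximal power output per kg from the exercise tests, and section 7.2.3 has weight recorded before each of them. Section 5.6.1 randomises within two age blocks.

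**The concern.** Where a parameter has its own baseline, section 9.9.1 adjusts for it. The race goes unadjusted only because it has no baseline race. A covariate need not be the same variable measured earlier; it only has to be measured before treatment and to predict the outcome. Baseline Pmax/kg is an obvious candidate. Entry is open above 4 W/kg and spans ages 18 to 50 (section 4.2), so riders may differ appreciably in fitness.

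The t-test leaves whatever part of those differences carries into the race in its error term. It also ignores the age blocks used in the allocation. If age predicts the outcome, its standard error is then somewhat larger than the design requires.

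At stake is the precision of the first-listed secondary objective (section 2.2), in the setting the trial was built to imitate. The timing matters too. Section 9.10 denies confirmatory value to data-driven analyses, so an adjustment chosen after unblinding would carry less weight than one fixed beforehand.

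**Working it through.** **Inputs from the protocol.** Two-sided alpha 0.05, unpaired t-test, 80% power, 22 per arm, SD 0.199 W/kg (section 1.4.9.2); 24 per arm enrolled (section 1.4.9.1); 1:1 allocation (section 1.4.5).

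**Input not in the protocol.** The correlation r between baseline Pmax/kg and the race outcome. It is taken here as an assumed range of 0.2 to 0.8.

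**Step 1: reproduce the protocol's nearest figure.** The protocol states no power for the race. For an unadjusted t-test with 22 per arm, the noncentral t distribution gives a detectable difference of 0.8646 SD. Multiplied by 0.199 this is 0.172 W/kg, the figure in section 1.4.9.2.

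**Step 2: effect of adjusting.** ANCOVA leaves a residual variance of (1 − r²) times the original. The detectable difference becomes 0.8646 × √(1 − r²), and the t-test would need 22 / (1 − r²) per arm to match it.

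| r | Variance left | Detectable difference, 22 per arm (SD) | Per-arm n for the t-test to match | Power for an assumed 0.5 SD effect |
|---|---|---|---|---|
| unadjusted | 1.00 | 0.86 | 22 | 37% |
| 0.2 | 0.96 | 0.85 | 23 | 38% |
| 0.3 | 0.91 | 0.82 | 24 | 40% |
| 0.5 | 0.75 | 0.75 | 29 | 47% |
| 0.7 | 0.51 | 0.62 | 43 | 62% |
| 0.8 | 0.36 | 0.52 | 61 | 77% |

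Simulating both tests (4,000 runs each, one covariate) gave ANCOVA power of 46%, 61% and 77% at r = 0.5, 0.7 and 0.8. With 24 per arm the unadjusted figure is 0.83 SD, and the adjusted ones are 0.72, 0.59 and 0.50 SD at the same three correlations.

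**Step 3: cost of estimating the covariates.** The formula in step 2 treats the covariate slopes as known. Two covariates reduce the error degrees of freedom from 42 to 40, which moves the critical value only from 2.018 to 2.021. Chance imbalance inflates the variance by about 1 + 2/(44 − 2 − 3) = 1.051, or 2.5% on the SD scale. Both together turn the five adjusted figures into about 0.87, 0.85, 0.77, 0.63 and 0.53 SD. Break-even is where (1 − r²) × 1.051 = 1, which is r of about 0.22. Blocking on age removes most of the imbalance in that covariate, so the true cost should be smaller.

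**The case against.** The strongest reply is that nothing here is wrong. Under randomisation the t-test is valid and unbiased, section 9.9.1 already requires estimates with 95% confidence intervals, and the race is a secondary objective in an exploratory trial. A detectable difference of 0.86 SD is also the standardised size that the protocol accepts for P/kg in section 1.4.9.2. All of this stands, and it limits the point to lost precision.

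A second reply is that r is unknown. If tactics and drafting largely decide the race, baseline Pmax/kg may predict it poorly and adjustment gains little. This stands too, and is why the range extends down to 0.2.

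A reader might infer more than the documents support:

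- **That total time covers the 150 km and a sampling stop.** Appendix 6 says "Subjects will climb the Mont Ventoux in an open course via Bédoin after a 150km closed course" and "A blood sample of each subject will be collected in Bédoin (at the end of the closed course) and at the finish". Nothing defines when the clock starts or whether it runs during sampling. Section 7.7 budgets eight haematology samples. Table 1 accounts for them as 1 at screening + 4 at dosing visits + 2 at the competition + 1 at follow-up. If the two competition samples are those at Bédoin and the finish, the timed race could be the climb alone.
- **That the protocol concedes the riders' times are not independent.** The remark in section 1.1.3, "combined with (team) tactics, the terrain and the effects of drag force", describes road racing over consecutive days and argues that VO2max is a poor proxy for performance. It says nothing about dependence between times in this one-day race.
- **That fitness drives most of the spread.** This needs r² above 0.5, so r above 0.71, and no figure in the protocol establishes it.

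**Conclusion.** The point holds as one of efficiency. The protocol commits single-measured race outcomes to an unadjusted test and leaves a plausible baseline predictor unused. The test is not biased, and it does not add variation; it fails to remove variation that could be removed.

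The size depends wholly on the assumed r. At 0.5 to 0.8, the difference detectable with 22 per arm falls from 0.86 SD to between 0.75 and 0.52 SD, equivalent to 1.3 to 2.8 times the sample size. At 0.2 to 0.3 it falls only to about 0.85 to 0.82 SD, and at 0.2 the cost of estimating two covariates can cancel the gain. The balance favours adjusting: the possible loss is about 2.5% on the SD scale, while the possible gain is large. The figures assume a linear relation, a common slope in both arms and 22 riders per arm with race data.

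**What to change.** In section 9.9.1, state that continuous race outcomes (time, power) are analysed by ANCOVA with treatment, baseline Pmax/kg and age stratum, with the unpaired t-test as supportive. Two details need naming:

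- **Which ramp test.** Use the pre-dose baseline test (day -14 to -1 in Table 1), not the familiarisation test at screening.
- **Which stratum.** Use the age block as randomised, because both bands in section 5.6.1 include age 34.

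The cost is two degrees of freedom, an assumption of linearity in Pmax/kg and a few lines of text. No new measurement is needed. Section 10.6.1 classes a change of statistical analysis as a non-substantial amendment. It should be made before the randomisation code is broken. The choice of race endpoint need not change for this.

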### **2.2 Secondary objectives**

To explore the effects of NeoRecormon on cycling performance in a competition (road race)

To evaluate the safety of NeoRecormon in well-trained cyclists

To evaluate the performance of doping detection methods for NeoRecormon use in well-trained cyclists

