#### **7.3.4 Blood flow**

LSCI measures:

- basal blood flow
- blood flow upon occlusion-reperfusion
- Blood flow after 'exercise'

Forearm blood flow will be measured by non-invasive laser speckle contrast imaging (LSCI; PeriCam PSI System, Perimed). At baseline and after 7 weeks of dosing, the flow will be measured at rest, during a five minute occlusion of the brachial artery and during reperfusion after the occlusion. Blood flow will be measured after exercise at 6 weeks. Procedures for LSCI, brachial artery occlusion-reperfusion are described in SOPs. Briefly, the subject will be seated with the left arm placed on a (table) rest. A suitable area of the volar side of the forearm will be identified. This area will be 'illuminated' by the laser and the response signal will be captured.

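### Section 9.9.1 analyses the once-measured race outcomes with an unadjusted t-test although a pre-dose fitness test exists for every rider, so the secondary race comparison gives up precision it could have for free

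*Protocol*

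**What the plan says.** Protocol section 9.9.1 has three rules for efficacy parameters. Repeated measures get a mixed-model ANCOVA with the baseline value as covariate. Parameters measured at baseline and at the end of treatment "will be analysed with a one-way ANCOVA with treatment and baseline as covariate". For the rest: "Single measured efficacy parameters will be analyzed with an unpaired t-test". Synopsis section 19 gives no other rule for single measures.

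The race is a secondary objective (section 2.2). It takes place once: "After the treatment period subjects will participate in a competition" (section 3.1.4). Section 6.1 lists among its outcomes the race result, "Total time of the race" and power in W. The third rule does not name the race, but no other rule fits it.

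On pre-treatment data, section 1.4.4 states: "A second ramp and TTE exercise test will be performed for baseline measurements within 2 weeks prior to the first administration". Appendix 5 describes the TTE test as a test of submaximal performance. Section 5.6.1 blocks the randomisation by two age bands in order to reduce variability between the arms. Section 4.2 admits men aged 18 to 50 with maximal power above 4 W/kg and sets no upper limit.

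**The concern.** Riders in such a group can differ considerably in fitness, and nothing in the randomisation balances fitness. The race ends with the Mont Ventoux climb (Appendix 6: 21.5 km, 1620 m), where power per kg should matter. An unadjusted comparison leaves all of that between-rider variation in the error term. It also ignores the age band on which the randomisation was blocked.

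The race is in the protocol because laboratory tests miss much of what decides real racing (section 1.4.8). If the confidence interval is wider than it need be, an inconclusive race result is more likely, and it may be misread as absence of effect.

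**Working it through.** **Inputs.** 24 per arm (section 1.4.7) and 22 after attrition (section 1.4.9.1); two-sided 5%; 80% power. Section 1.4.9.2 gives 5.2 W/kg at 80% of VO2max in professionals, SD 0.199, and a detectable difference of 0.172. The protocol gives no SD for any race outcome and no correlation ρ between baseline fitness and race outcome. I therefore take ρ from 0.3 to 0.9 as an assumed range.

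**The plan's own figure.** No power is stated for the race. The nearest figure is the 0.172 W/kg. A two-sample t-test with 22 per arm detects 0.865 SD with 80% power, and 0.865 × 0.199 = 0.172, so that figure reproduces with 22 evaluable riders per arm.

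**Unadjusted race comparison.** The detectable difference is about (t₀.₉₇₅ + t₀.₈₀) × √(2/n). With 24 per arm and 46 degrees of freedom this is (2.013 + 0.850) × √(2/24) = 2.863 × 0.2887 = 0.83 SD. The noncentral t gives the same.

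**Adjusted comparison.** A covariate with within-arm correlation ρ multiplies the residual SD by √(1 − ρ²). The power is that of a noncentral t with noncentrality d/√(1 − ρ²) × √(n/2). The model with treatment, covariate and age stratum leaves 48 − 4 = 44 degrees of freedom. No gain is credited to the stratum.

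| ρ (assumed) | √(1 − ρ²) | Detectable, 24/arm (SD) | Detectable, 22/arm (SD) | Power at 0.5 SD, 24/arm | Equivalent sample size, 1/(1 − ρ²) |
|---|---|---|---|---|---|
| t-test | 1 | 0.83 | 0.86 | 40% | 1.0 |
| 0.3 | 0.954 | 0.79 | 0.83 | 43% | 1.1 |
| 0.5 | 0.866 | 0.72 | 0.75 | 50% | 1.3 |
| 0.7 | 0.714 | 0.59 | 0.62 | 66% | 2.0 |
| 0.8 | 0.600 | 0.50 | 0.52 | 81% | 2.8 |
| 0.9 | 0.436 | 0.36 | 0.38 | 97% | 5.3 |

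**Price of adjusting.** Losing two degrees of freedom changes the detectable difference by about 0.1%. Chance imbalance in the covariate adds on average a variance factor of about 1 + 1/44 = 1.023, or roughly 1% on the SD scale; the table leaves this out. Adjustment breaks even at ρ² = 1/45, that is ρ of about 0.15.

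**Scale of a relevant effect.** On the professional SD, 0.172/0.199 = 0.86 SD, and the t-test with 24 per arm has 83% power. If the trial's riders vary more, the same difference is a smaller fraction of an SD. With an assumed SD of 0.3 it is 0.172/0.3 = 0.57 SD, and with 0.5 it is 0.34 SD. The noncentral t then gives the t-test 49% and 21% power; adjustment at ρ = 0.7 raises these to 78% and 37%. This carries a difference in submaximal laboratory power over to the race, which is itself an assumption.

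**Validity.** Simulated type I error of the t-test was 4.9% to 5.2% for ρ of 0, 0.7 and 0.9. The chance difference between arms in baseline fitness has standard error √(2/24) = 0.29 SD (95% range ±0.57 SD). The t-test's confidence interval already allows for it.

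**The case against.** The strongest objection is that this concerns efficiency in an exploratory secondary objective, and that its size is unknown. That stands. At ρ = 0.3 the detectable difference only moves from 0.83 to 0.79 SD. Low values are plausible: the climb follows a 150 km closed course, race time is not stated to be climb time, and section 1.1.3 itself says that tactics, terrain and drag shape racing. Blocking by age also removes some imbalance between the arms. None of this is a reason to leave the covariate out, since adjustment costs about 1% at worst.

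Four stronger readings are tempting, and the documents do not support them:

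- **Fitness differences dominate the race comparison.** Fitness explains more than half the variance only if ρ exceeds √0.5 = 0.71, and the protocol gives neither ρ nor a race SD.
- **The noise exceeds the effect that the protocol treats as relevant.** On the only SD documented, the effect is 0.86 SD, against a 95% half-width of 2.013 × 0.289 = 0.58 SD. The reading needs a wider spread, which is plausible for this entry criterion but not stated.
- **The race is the one efficacy outcome without baseline adjustment.** Appendix 5, section 18.3, also specifies ANOVA and unpaired t-tests without a baseline covariate for exercise-test parameters.
- **Blood flow needs the same change.** Section 7.3.4 says "Blood flow will be measured after exercise at 6 weeks", and the baseline flow is taken at rest and around occlusion. Nothing in the protocol shows that resting flow predicts flow after exercise.

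Race power in plain W is a unit of measurement and no defect in itself. Weight is recorded before each exercise test (section 7.2.3), so power per kg can be derived.

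**Conclusion.** The point holds as a loss of precision. Section 9.9.1 fixes an unadjusted test for race time and race power, while a pre-dose fitness measure and the age stratum are available for every rider. The analysis as written remains valid. For ρ between 0.5 and 0.8, adjustment lowers the detectable difference by 13% to 40% (factors 0.866 and 0.600); over the full assumed range of 0.3 to 0.9 the reduction is 5% to 56%. These figures assume that all 24 per arm race, that the covariate relation is linear with the same slope in both arms, and that ρ lies in a range the protocol does not document. The change is worth making because the possible gain is large and the possible loss negligible.

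**What to change.** In section 9.9.1, qualify the rule for single measures along these lines:

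> Total race time and race power per kg (weight from the last ramp test) will be analysed by ANCOVA with treatment, baseline maximal power per kg from the pre-dose ramp test, and the age stratum as randomised. An unpaired t-test will be reported as a supportive analysis. Other single measures without a pre-dose predictor will be analysed with an unpaired t-test. Finishing position, if analysed, will be compared by a rank-based method.

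The words *as randomised* matter because both age bands in section 5.6.1 include age 34. The covariate should be fixed before unblinding, so that it cannot be chosen after seeing the race results.

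The cost is two degrees of freedom and no new data. Section 10.6.1 classes a change of statistical analysis as a non-substantial amendment.
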